## Abstract

**Introduction:**

Non-alcoholic fatty liver disease (NAFLD) affects approximately one in four individuals and its prevalence continues to rise. The advanced stages of NAFLD with significant liver fibrosis are associated with adverse morbidity and mortality outcomes. Currently, liver biopsy remains the ‘gold-standard’ approach to stage NAFLD severity. Although generally well tolerated, liver biopsies are associated with significant complications, are resource intensive, costly, and sample only a very small area of the liver as well as requiring day case admission to a secondary care setting. As a result, there is a significant unmet need to develop non-invasive biomarkers that can accurately stage NAFLD and limit the need for liver biopsy. The aim of this study is to validate the use of the urine steroid metabolome as a strategy to stage NAFLD severity and to compare its performance against other non-invasive NAFLD biomarkers.

**Methods and analysis:**

The TrUSt-NAFLD study is a multicentre prospective test validation study aiming to recruit 310 patients with biopsy-proven and staged NAFLD across eight centres within the UK. 150 appropriately matched control patients without liver disease will be recruited through the Oxford Biobank. Blood and urine samples, alongside clinical data, will be collected from all participants. Urine samples will be analysed by liquid chromatography-tandem mass spectroscopy to quantify a panel of predefined steroid metabolites. A machine learning-based classifier, for example, Generalized Matrix Relevance Learning Vector Quantization that was trained on retrospective samples, will be applied to the prospective steroid metabolite data to determine its ability to identify those patients with advanced, as opposed to mild-moderate, liver fibrosis as a consequence of NAFLD.

**Ethics and dissemination:**

Research ethical approval was granted by West Midlands, Black Country Research Ethics Committee (REC reference: 21/WM/0177). A substantial amendment (TrUSt-NAFLD-SA1) was approved on 26 November 2021.

**Trial registration number:**

ISRCTN19370855.

STRENGTHS AND LIMITATIONS OF THIS STUDYThe participants recruited with non-alcoholic fatty liver disease will all have had a liver biopsy to stage their disease severity as well as multiple other non-invasive biomarkers that are currently used in clinical practice.The study includes a well-matched and phenotyped control cohort without evidence of liver disease, prospectively recruited from an existing biobank.A urinary test has high patient acceptability and is less operator dependent than other non-invasive tests such as transient elastography.The study is cross-sectional and not longitudinal, so will not be able to address questions as to the utility of biomarker strategies and disease progression/remission.The study will recruit patients having a liver biopsy as part of routine clinical care which may introduce a degree of selection bias, creating a cohort more likely to have advanced (as opposed to mild) disease severity.

## Introduction

Non-alcoholic fatty liver disease (NAFLD) is the most prevalent chronic liver condition.^1^ It affects up to 30% of the population (rising to 60% of patients with diabetes and obesity); >50 million adults in Europe and >10 million adults in the UK. It is the second most common indication of liver transplantation worldwide^2 3^ and now accounts for 8.4% of liver transplants in Europe.^4^ The advanced stages are associated with a fourfold to fivefold increase in mortality and morbidity, driven through liver-specific causes (including hepatocellular carcinoma (HCC)) and cardiovascular events.^5 6^ Estimates suggest that NAFLD costs the UK in excess of £5 billion per year and, globally, the expected 10-year burden of NAFLD could exceed $1.005 trillion in the USA and €334 billion in Europe.^7^

NAFLD is a spectrum of disease ranging from simple steatosis through to inflammation (non-alcoholic steatohepatitis) to fibrosis (graded from F0 to F4) with the risk of cirrhosis (F4) and the development of HCC. Fibrosis stage is tightly associated with an adverse clinical outcome with both liver-specific and cardiovascular morbidity and mortality.^8 9^ The current reference standard for assessment of NAFLD severity is liver biopsy; however, there are significant complications and poor patient acceptability.^10 11^ In addition, it is a resource-intensive and costly procedure, requires day case admission and time off work for the patient, samples a very small area of the liver and the interpretation of the biopsy findings is fraught with interindividual variability.^12^ Therefore, the development of accurate, non-invasive markers to stage NAFLD is a critical unmet priority clinical need. Routine interpretation of liver biochemistry is unhelpful; 50% of patients with advanced fibrosis (F3 or F4) have normal liver chemistry.^13^ Several non-invasive tools (serological, clinical, imaging) have been developed; however, to date, none have been shown to be sufficiently robust to replace liver biopsy.^14^

The liver is the main site of steroid metabolism and there is disruption of specific pathways in patients with NAFLD,^15 16^ providing biological plausibility to our approach. The pilot study showed an increased activity in 11β-hydroxysteroid dehydrogenase type 1 and 5α reductase in patients with advanced fibrosis.^17^ Steroid 5β reductase (AKR1D1), which is mostly expressed in the liver, has also been shown to decrease as fibrosis in NAFLD progresses.^16^ When coupled with machine learning-based analysis using, for instance, Generalized Matrix Learning Vector Quantization (GMLVQ), a global assessment of hepatic steroid hormone metabolism can be made. GMLVQ is a supervised machine learning technique whereby an algorithm is trained using known datasets, and then subsequently applied to unknown samples. GMLVQ is able to simplify complex data into clusters of patients who have a high risk of having advanced fibrotic NAFLD. Data from our published proof-of-principle study indicate that this is tightly influenced by NAFLD stage.^17^ As part of this discovery study, we analysed urine samples from 227 subjects (121 with biopsy-proven NAFLD and 106 controls). GMLVQ analysis achieved excellent separation of early (F0–F2) from advanced (F3–F4) fibrosis (area under the curve-receiver operating characteristic curve (AUC-ROC): 0.92 (0.91–0.94)). There was near perfect separation of healthy controls from patients with advanced fibrotic NAFLD and from those with NAFLD cirrhosis. Further refinement of the model incorporated the 10 most discriminatory steroids as well as patient age and body mass index (BMI) which has further enhanced diagnostic performance.^17^

The aim of the current study is to prospectively validate our published findings in an independent cohort of patients undergoing routine liver biopsy for NAFLD and to compare the performance of the machine learning-based urine steroid metabolome test against other non-invasive biomarker strategies that are currently used in clinical practice.

## Methods and analysis

### Design

TrUSt-NAFLD is a prospective, observational, non-interventional clinical study where recruitment and participation is designed to coincide with routine National Health Service (NHS) clinical care aiming to avoid the need for additional venepuncture, minimise inconvenience to participants and maximise recruitment potential. Occasionally, additional study-specific visits for participants will be scheduled where this can facilitate recruitment or ensure that samples are collected within the predefined time limitations of the study (samples collected within 12 months of liver biopsy).

A dedicated control cohort of participants without evidence of liver disease will be prospectively recruited from an existing biobank of patients (Oxford Biobank (OBB), https://www.oxfordbiobank.org.uk) who have undergone detailed metabolic phenotyping and provided consent to be recalled by phenotype for additional clinical studies. These participants will not undergo liver biopsies but will have a comprehensive assessment of non-invasive NAFLD biomarkers measured as well as urine steroid metabolite analysis.

### Setting and participants

The study will take place in secondary care hospital settings in eight dedicated hepatology clinics across the UK. Patients (male or female) aged ≥18 years, who are attending or have attended an NHS clinic for the diagnosis and/or management of NAFLD and who are scheduled to have a liver biopsy or who have had a liver biopsy to stage NAFLD within the last 12 months will be approached to participate. Control participants without evidence of NAFLD will be recruited from the OBB based at the Oxford Centre for Endocrinology, Diabetes and Metabolism, Churchill Hospital, Oxford, UK.

### Patient and public involvement

The study protocol and associated supporting documentation was reviewed by a dedicated patient and public involvement panel that is supported by the National Institute for Health and Care Research (NIHR) Oxford Biomedical Research Centre (BRC) and their feedback was incorporated into the final study documents. The panel will continue to be involved with dissemination activities following study completion.

### Recruitment

The TrUSt-NAFLD study will recruit patients with a diagnosis of NAFLD from dedicated NHS hepatology clinics. The initial approach for participants to be part of the study will be made by members of the team directly involved in their clinical care. In some situations, an alternative recruitment strategy whereby patients (who have consented to be approached for future research) are contacted having been identified from existing clinical databases may be employed. To ensure sufficient recruitment of patients, eight centres across the UK will participate in the study. Interested potential participants will be seen during their routine NHS clinic visit by the research team to confirm eligibility. Those patients identified from existing databases will be contacted by letter and their eligibility will have been assessed prior to contact by lead clinicians and researchers within the dedicated hepatology team.

Recruitment of control participants without NAFLD will use the OBB; a biobank of >9000 volunteers in Oxfordshire, UK, who have undergone extensive metabolic phenotyping and consented to be reapproached for clinical research. In order to try to ensure the absence of significant liver disease, individuals with a Homeostatic Model Assessment for Insulin Resistance (HOMA-IR) (as a marker of global insulin resistance) (https://www.dtu.ox.ac.uk/homacalculator/) in the lowest 25%, BMI <35 kg/m^2^ and fasting triglyceride levels <2 mmol/L will be invited to participate. HOMA-IR, triglycerides and BMI are all measured and recorded as part of the detailed OBB metabolic phenotyping and therefore can be used in a recall-by-phenotype strategy. Invitations to take part in the study will be sent with an aim of recruiting 60% male and 40% female participants to match the anticipated sex distribution in the NAFLD cohort which has been estimated from local liver biopsy data. Only individuals with normal liver biochemistry and non-invasive serum markers (including the enhanced liver fibrosis (ELF) panel) indicating low risk of advanced NAFLD will be included in the study.

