#### Control participants without evidence of NAFLD

Participant is willing and able to give informed consent for participation in the study.Bottom 25th percentile of HOMA-IR in OBB.BMI <35 kg/m^2^.Fasting triglycerides <2.0 mmol/L.Aged ≥18 years.

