### Exclusion criteria

#### All participants

Insufficient understanding of written and verbal English.The participant has not had sufficient time to read the PIL and understand the study requirements.Hepatic steatosis, inflammation or fibrosis with a primary aetiology other than NAFLD.

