For all participants, demographic data will be collected including age, sex, ethnicity, height, weight and calculated BMI. Details of the participants’ clinical history will also be collected, including any relevant medical history (smoking, type 2 diabetes, hypertension, cardiovascular disease and alcohol use) as well as details of concomitant prescribed medications. Patients with NAFLD will usually have routine blood tests as part of their clinical care consultation and therefore the additional blood samples that will be collected will not require additional venepuncture (although this may be needed if a participant attends for a dedicated research visit that is separate from their clinical care appointment). A dedicated research visit is required for all participants without NAFLD that will include collecting demographic data and clinical history as well as venepuncture and providing a 10 mL urine sample. Vibration-controlled transient elastography (VCTE) is frequently used in hepatology clinics to determine the risk of advanced fibrosis and can provide both a measure of liver stiffness (indicative of fibrosis stage) and a controlled attenuation parameter that correlates with the degree of hepatic steatosis.^18 19^ Where available, these data will be recorded for all patients with NAFLD.

All blood sample analyses will include measurement of a full blood count, renal function and electrolytes, liver chemistry (including alanine aminotransaminase (ALT), aspartate aminotransaminase (AST), alkaline phosphatase, gamma-glutamyltransferase, bilirubin, albumin, ferritin), total and high-density lipoprotein-cholesterol and triglycerides as well as glycated haemoglobin. In addition, samples will be analysed for the ELF panel^20^ (hyaluronic acid, type III procollagen peptide and tissue inhibitor of matrix metalloproteinase 1). Calculations for non-invasive risk score to detect advanced fibrosis will also be made including NAFLD Fibrosis Score (NFS), Fib-4, AST to Platelet Ratio Index (APRI), Fibroscan-AST (FAST) and BMI, AST/ALT Ratio, Diabetes Mellitus (BARD) .^21–25^

Liver biopsy data will be collected to include the NAFLD Activity Score grading with its individual components of steatosis, lobular inflammation, and ballooning and also the fibrosis staging (graded F0–F4) according to the Kleiner classification.^26^

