### Analysis of outcome measures

Data for all participants who complete the study will be included in the analysis. If any participants withdraw from the study, samples and data collected will not routinely be destroyed and will be used in the analysis unless requested not to do so by the individual. Statistical analysis will be undertaken at the end of study and after the analysis of all the samples has been completed.

The primary outcome of the TrUSt-NAFLD study is to determine the accuracy of the urine steroid metabolome GMLVQ algorithm to distinguish early (F0-2) from advanced (F3–F4) NAFLD fibrosis. Sensitivity, specificity and negative and positive predictive values will be calculated with 95% CIs. Additionally, ROC curves will be generated and the AUC will be calculated.

Secondary and exploratory outcomes will include a comparison of the performance of the urine steroid metabolome GMLVQ algorithm against other non-invasive NAFLD biomarkers (Fib-4, NFS, BARD, APRI, AST/ALT, ELF, FAST, VCTE). Data from participants with NAFLD will also be compared against control participants without evidence of NAFLD to determine the ability of the algorithm to detect NAFLD (across the spectrum of its severity) in the general population. Finally, exploratory analyses detecting steroid metabolites using LC-MS-MS in serum samples and subsequently incorporating the GMLVQ algorithm will be performed and compared against the urine analysis.

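### Controls are screened for low risk of advanced NAFLD but serve as the negatives for detecting NAFLD of any severity in the general population, a claim that the comparison cannot support as worded

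*Protocol article*

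**What the plan says.** All references are to the protocol article.

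**How controls are chosen.** The control inclusion criteria give a metabolic filter: "Bottom 25th percentile of HOMA-IR in OBB", with limits on BMI (below 35 kg/m²) and fasting triglycerides (below 2.0 mmol/L). The Recruitment section states the purpose of that filter: "In order to try to ensure the absence of significant liver disease". It then adds a blood-test screen: liver chemistry must be normal, and only people with "non-invasive serum markers (including the enhanced liver fibrosis (ELF) panel) indicating low risk of advanced NAFLD will be included in the study".

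**What is measured in them.** Under Design: "These participants will not undergo liver biopsies but will have a comprehensive assessment of non-invasive NAFLD biomarkers measured". Under Study procedures, the control visit consists of demographic data, clinical history, blood and urine. That section describes transient elastography with its controlled attenuation parameter, which tracks steatosis, and adds: "Where available, these data will be recorded for all patients with NAFLD". Nothing equivalent is stated for controls. The exclusion criterion on liver disease, shared by both cohorts, is "Hepatic steatosis, inflammation or fibrosis with a primary aetiology other than NAFLD".

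**How they are used.** Under Analysis of outcome measures, among the secondary and exploratory outcomes, data from NAFLD participants will be "compared against control participants without evidence of NAFLD to determine the ability of the algorithm to detect NAFLD (across the spectrum of its severity". The sentence ends by referring this ability to the general population. The Abstract is less guarded about the same people: "150 appropriately matched control patients without liver disease will be recruited through the Oxford Biobank".

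**The concern.** The negative state that the comparison needs is absence of any NAFLD. The Introduction describes NAFLD as a spectrum that begins at simple steatosis. The stated screening aims are absence of significant liver disease and low risk of advanced NAFLD. A control could therefore meet every stated criterion and still have simple steatosis or early fibrosis.

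If some controls do, those whom the algorithm flags are counted as false positives although the test was right. Those whom it misses are counted as true negatives although the test was wrong. Either way, specificity and AUC for any NAFLD are not estimated against the condition named, and the problem is greatest at the early end of the spectrum. At stake is whether the paper can report accuracy for detecting NAFLD at all severities in the general population.

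**Working it through.** **The plan's own figure.** The Sample size section states no precision or power for the control comparison. Its 85% power concerns sensitivity of 80% versus 92% among NAFLD patients, with 310 × 0.5 = 155 at F3–F4. With independent test results, the discordant probabilities are 0.92 × 0.20 = 0.184 and 0.80 × 0.08 = 0.064, summing to 0.248. McNemar power at two-sided 5% is Φ[(0.12√155 − 1.96√0.248)/√(0.248 − 0.12²)] = Φ(1.07) = 85.8%. The stated figure reproduces. It uses no controls, so this point does not touch it.

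**Do the stated criteria exclude NAFLD steatosis in a control?**
- Metabolic filter: makes steatosis less likely, but does not measure it, and BMI up to 35 kg/m² is allowed.
- Normal liver biochemistry: the Introduction says half of patients with advanced fibrosis have normal liver chemistry, so this alone does not exclude disease.
- ELF and other serum markers: stated as indicating low risk of advanced disease.
- Exclusion criterion: removes steatosis only when its main cause is something other than NAFLD.
- Elastography: stated for NAFLD patients only.

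The biochemistry and serum-marker requirement appears under Recruitment and not in the inclusion list. I take it, in the plan's favour, as applied to every control.

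**Size of the misclassification component.** Inputs: n = 150 controls (Sample size). Assumed, because the article gives none of them: share m of controls with undetected NAFLD, true specificity Sp = 95%, and sensitivity for early NAFLD Se = 30–70%.

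Observed specificity = (1 − m)·Sp + m·(1 − Se), so the loss is m·(Sp + Se − 1).

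SE = √(0.95 × 0.05 / 150) = 1.78 points.

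| m | Loss, Se = 30% | Loss, Se = 50% | Loss, Se = 70% |
|---|---|---|---|
| 2% | 0.5 | 0.9 | 1.3 |
| 5% | 1.25 | 2.25 | 3.25 |
| 10% | 2.5 | 4.5 | 6.5 |
| 20% | 5.0 | 9.0 | 13.0 |

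Losses are in percentage points. At m = 5% they are 0.7–1.8 SE (Se 30–70%), and at m = 10% they are 1.4–3.7 SE. With Sp = 90% and Se = 30–80%, the losses are 1.0–3.5 points at 5% and 2.0–7.0 at 10%. With m = 0 there is no loss. The Introduction's figure of up to 30% of the population is a ceiling for unselected people; the filters should bring m below it.

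**AUC.** Suppose a true AUC of 0.85 (assumed).
- If mislabelled controls score like cases in general, observed AUC = 0.85(1 − m) + 0.5m, a loss of 0.35m: about 0.018 at 5% and 0.035 at 10%.
- If they score like F0–F2 patients, and half the cases are F3–F4 and separated from F0–F2 with the pilot AUC of 0.92, their AUC against cases is 0.5 × 0.5 + 0.5 × 0.92 = 0.71. The loss is then 0.14m: 0.007 and 0.014.

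**The opposing effect.** Let Sp_gp be specificity in NAFLD-free members of the general population. Observed specificity minus Sp_gp equals (Sp − Sp_gp) − m(Sp + Se − 1). The first term is positive if metabolically very healthy people test negative more often than other NAFLD-free people. At m = 5% and Se = 70%, Sp_gp = 95 − 3.25 = 91.75% makes the two terms cancel; a lower Sp_gp makes the observed figure too high. The article gives neither term.

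**The case against.** The metabolic filters are not tests for advanced fibrosis. Low insulin resistance, limited BMI and low triglycerides all reduce the chance of steatosis, so a reader who infers that controls are screened only against advanced disease goes too far. That stands.

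Much of the wording is also hedged. Several sections say without evidence of NAFLD or of liver disease, and the Discussion admits that controls cannot ethically be biopsied. The shared exclusion criterion has to spare NAFLD for the patient cohort, so it is weak evidence about who enters as a control. The Introduction's figure on normal liver chemistry concerns advanced fibrosis, not people who have passed every filter. These points soften the contradiction but do not close it. No stated measurement looks for steatosis in controls, the Abstract drops the hedge, and the Discussion's caveat does not mention misclassified steatosis.

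The magnitude rests on assumed inputs. Even the 3.25-point loss at m = 5% is within the 95% half-width of 1.96 × 1.78 = 3.5 points. That is a reason for a sensitivity range instead of a single correction.

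A misclassification analysis might sit in a statistical analysis plan that is not shown. Its absence from the article is therefore not the finding. The finding is that the stated selection and the stated claim do not match.

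**Conclusion.** The mismatch is real and confined to a secondary or exploratory comparison. The control criteria make undetected NAFLD less likely without ruling it out, and the article then uses these people as negatives for NAFLD of every severity. Misclassification alone would cost about 1.3–3.3 points of specificity at 5% undetected NAFLD and 2.5–6.5 points at 10%, if specificity is 95% and early-stage sensitivity 30–70%.

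A reader might infer that specificity and AUC are therefore biased downward overall, with undetected steatosis simply becoming false positives. The documents do not support that. Only test-positive mislabelled controls become false positives; the rest conceal misses. Selection of metabolically very healthy controls pulls towards optimism when the claim is about the general population, so the net direction is unknown. Either way, the general-population wording is not supported by this control group.

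**What to change.** 1. Under Analysis of outcome measures, keep the planned NAFLD-versus-control comparison, overall and by fibrosis stage. State what it estimates: discrimination of NAFLD from metabolically healthy, unbiopsied controls at low risk of advanced NAFLD. Drop the claim of detection accuracy in the general population.
2. In the Abstract, describe the controls with that same label in place of the statement that they have no liver disease.
3. For the any-NAFLD and F0–F2 contrasts, report specificity and AUC with a sensitivity analysis over an assumed 0–20% undetected NAFLD in controls. For specificity, the corrected value is (observed − m(1 − Se))/(1 − m), across a range of Se.
4. Exclude from the control set anyone whose collected clinical history records steatosis or NAFLD.

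F3–F4 versus controls should not be promoted to the main control contrast. It is an extreme-group comparison, already reported as near perfect in the pilot, and would sidestep the question the study asks.

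The cost is a change of wording and a short extra analysis, with no new participants or procedures. The downside is a narrower claim from the control cohort.
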